### Data Monitoring and Management of Adverse Events

An independent researcher, blinded to group allocation, will be responsible for monitoring, recording, and reporting any adverse effects or discomfort, as well as for database management and statistical analyses. Participants will be instructed to immediately report any adverse events, which will be documented and classified according to severity and possible relation to the intervention. For safety, blood pressure, heart rate, and any adverse symptoms will be monitored during every session. Criteria for withholding or interrupting training have been established, such as excessively high or low blood pressure, discomfort or pain preventing performance, or ineffective medication. The principal examiner will supervise all exercise sessions, monitoring exercise intensity, participants’ safety, and adherence to the program. Decisions regarding whether an adverse event is related to the intervention will be made based on clinical judgment and temporal association with the exercise sessions. The trial will be temporarily suspended or terminated prematurely if serious adverse events occur that are deemed directly related to the intervention, or if safety concerns arise that cannot be mitigated. All participants will receive prior guidance to ensure a safe home environment before initiating the intervention. All adverse events will be reported to the institutional research ethics committee of the Universidade Federal de Minas Gerais in accordance with established guidelines.

### Sample Size

The sample size calculation was performed considering the primary outcome measure, bradykinesia (assessed using items 3.8, 3.9, 3.10, and 3.14 of the motor examination of the MDS-UPDRS) [25] based on data provided by a previous similar randomized controlled trial. The effect size for bradykinesia was derived from the study of Ni et al [11]. On the basis of a previous study [11] reporting a mean difference of –2.3 (SD 2.5), a sample size of 40 participants was required to achieve a power of 0.80 at a 2-tailed significance level (α=.05). Assuming a dropout rate of 15%, 46 participants will be recruited (23 per group).

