### Participants

Individuals will be recruited from the community through contact with health centers, research groups, university extension programs, and dissemination on social media. Individuals who express interest in participating will be contacted by a member of the research team and will be provided with detailed information about the study objectives, procedures, and eligibility criteria.

Eligibility will be determined through a 2-step screening process. An initial screening interview will be conducted by telephone to verify key inclusion and exclusion criteria. Individuals who meet the preliminary criteria will be invited to attend an in-person baseline assessment, during which clinical eligibility will be confirmed and written informed consent will be obtained prior to enrollment in the study.

Individuals will be included if they are 50 years or older, have idiopathic PD diagnosed by a neurologist, are classified between stages 1 to 3 of the modified Hoehn and Yahr Scale [24], present bradykinesia identified by items 3.8 and/or 3.14 of the motor examination of the Movement Disorder Society–sponsored revision of Unified Parkinson’s Disease Rating Scale (MDS-UPDRS) [25], are taking antiparkinsonian medication and are medically stable, are classified as inactive or insufficiently active [26], have the ability to walk independently without assistive devices, and have written medical permission to participate in the study. Bradykinesia will be established if participants score at least 1 point (out of 4) on item 3.8 (leg agility) and/or item 3.14 (global spontaneity of movement–body bradykinesia) of the MDS-UPDRS, which are validated measures of bradykinesia in PD [25]. Physical activity status will be determined using the Centers for Disease Control and Prevention classification: individuals reporting no exercise will be classified as inactive, whereas those performing insufficient exercise will be classified as insufficiently active [26].

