### Primary Outcome Measure

Bradykinesia of the lower limbs will be measured using item 3.8 (leg agility), assessed bilaterally (right and left), and item 3.14 (global spontaneity of movement–body bradykinesia) of the motor examination of the MDS-UPDRS [25]. Each score ranges from 0 to 4, with 0 indicating normal function and 4 indicating severe impairment [25]. The primary bradykinesia outcome will be calculated as the sum of the bilateral scores for item 3.8 and the score for item 3.14, resulting in a composite score ranging from 0 to 12. Higher scores indicate more severe bradykinesia [28].

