### Statistical Analyses

All statistical analyses will be performed by an independent examiner blinded to group allocation using SPSS for Windows (IBM Corp). Baseline characteristics will be summarized by treatment group using descriptive statistics. Means (SD) or median (IQR) will be used for continuous variables according to analysis of normality (Shapiro-Wilk test). Frequency (percentage) will be used for categorical variables.

All analyses will follow the intention-to-treat principle, including all randomized participants in the groups to which they were originally allocated. The primary outcome will be the lower limb bradykinesia score, with the primary end point defined as the postintervention assessment at 12 weeks. Analytic approaches will be used to handle missing data, as recommended by Jakobsen et al [37]. The specific procedure will depend on the proportion of missing data, as stated by Jakobsen et al [37]. The statistical models will include a random intercept for participants and fixed effects for time (before intervention, after intervention, and follow-up), group (intervention and control), and group-by-time interaction. The primary analysis will focus on the group-by-time interaction effect. The level of significance will be set at 5%. Effect estimates will be reported considering the CIs (95% CI) for the between-group mean differences at each time point (week 12 minus week 0 and week 16 minus week 0). Secondary outcomes will be considered exploratory. Where applicable, adjustment for multiple comparisons will be performed using the Bonferroni method [38].

Adverse events will be summarized descriptively by treatment group, including the number and proportion of participants experiencing at least one event, as well as the frequency and severity of events.

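### The sample size is computed for a four-item bradykinesia score, but the primary outcome is a different 0-12 score, so 0.80 power is not established for the outcome tested

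*Protocol article*

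**What the plan says.** Three sections of the protocol article describe the primary outcome.

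- **Sample Size** says the calculation was done for the primary outcome measure, given as "bradykinesia (assessed using items 3.8, 3.9, 3.10, and 3.14 of the motor examination of the MDS-UPDRS"). From a previous trial it takes "a mean difference of –2.3 (SD 2.5), a sample size of 40 participants was required to achieve a power of 0.80" at two-tailed alpha 0.05. With 15% allowed for dropout, 46 are to be recruited, 23 per group.
- **Primary Outcome Measure** gives this scoring rule: "sum of the bilateral scores for item 3.8 and the score for item 3.14, resulting in a composite score ranging from 0 to 12".
- **Statistical Analyses** agrees with that definition: "The primary outcome will be the lower limb bradykinesia score, with the primary end point defined as the postintervention assessment at 12 weeks".

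Items 3.9 and 3.10 appear only under Sample Size. The Results section reports that 46 participants were enrolled and that no analysis has yet been done.

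**The concern.** Two item sets are given for one primary outcome. The only effect and SD in the article are attached to the set that will not be tested, and nothing explains why they should hold for the other.

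Two things are at stake. First, a null result on the 0-12 score would be read against a power of 0.80 that was never shown for that score, and -2.3 points would be taken as its target difference without support. Second, with two definitions in the published protocol, a reader of the results cannot tell whether the score reported was the one planned, which invites a question about outcome switching.

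**Working it through.** **Inputs (Sample Size section).** Difference 2.3, SD 2.5, two-sided alpha 0.05, power 0.80, 40 evaluable (20 per arm at 1:1), 46 recruited (23 per arm). All power figures below are for a two-sample t-test (noncentral t).

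**Step 1: reproduce the plan's figure.**
d = 2.3 / 2.5 = 0.92. Power 0.80 needs 19.55, so 20 per arm and 40 in total. Power at 20 per arm is 0.809. The stated 40 reproduces. The calculation is sound for its inputs, and the question is whether those inputs belong to the outcome tested.

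**Step 2: compare the two definitions.**

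| Rating | Sample Size | Primary Outcome Measure |
|---|---|---|
| 3.8 | yes (sides not stated) | yes, right and left |
| 3.9 | yes | no |
| 3.10 | yes | no |
| 3.14 | yes | yes |
| Range | not stated | 0 to 12 (3 ratings × 4) |
| Effect and SD | -2.3 (SD 2.5) | none given |

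**Step 3: when would 0.80 carry over?** Solve for the d that gives power 0.80.

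- 20 and 20 per arm: d = 0.909
- 23 and 23 per arm (all 46 analysed, equal split): d = 0.845
- 19 and 20 (46 × 0.85 = 39.1, so about 39 completers): d = 0.922

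The claim therefore holds for the 0-12 score only if its standardized effect is about 0.91 or more with 20 per arm, or about 0.84 with 23 per arm.

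**Step 4: illustration under stated assumptions.** Suppose the four-item score is the sum of five 0-4 ratings (3.8 right, 3.8 left, 3.9, 3.10, 3.14) with equal effects, equal variances and common correlation r, and that -2.3 (SD 2.5) refers to that sum. Keeping three ratings gives:

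- difference = 2.3 × 3/5 = 1.38
- SD = 2.5 × √[(3 + 6r) / (5 + 20r)]

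| r | SD | d = 1.38/SD | Power, 20 per arm | Power, 23 per arm |
|---|---|---|---|---|
| 0 | 1.94 | 0.71 | 0.59 | 0.66 |
| 0.3 | 1.65 | 0.84 | 0.73 | 0.79 |
| 0.5 | 1.58 | 0.87 | 0.77 | 0.83 |
| 0.8 | 1.52 | 0.91 | 0.80 | 0.85 |

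**Step 5: the result depends on the assumptions in both directions.** If the SD of the 0-12 score were 2.0, power with 20 per arm would be 0.94 for a difference of 2.3 (d = 1.15), 0.64 for 1.5 (d = 0.75) and 0.34 for 1.0 (d = 0.50). The article supplies nothing with which to choose among these.

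**The case against.** The strongest reply is that the calculation depends only on d = 0.92, which has no units. If the standardized effect is similar on the lower limb score, the sample size stands. That is fair: the article does not show that power is below 0.80. With all 46 analysed, the illustration gives 0.79 at r = 0.3 and 0.83 at r = 0.5. If the lower limb items respond more strongly to lower limb training, power would be higher still. What remains is that the article neither states nor justifies this transfer.

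A second reply is that little depends on the figure now. Recruitment is closed, two sections agree on the lower limb score, no decision rule uses the power, and 95% confidence intervals will show the precision achieved. This limits the damage but does not remove the contradiction.

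Three stronger readings are tempting, and the documents do not support them.

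- *The -2.3 (SD 2.5) belongs to a longer scale and cannot be carried over.* The article does not say on which score the previous trial reported it. The item list describes this trial's own outcome.
- *A 2.3-point gain is out of reach because participants can enter with a total of 1.* Entry requires a "score at least 1 point (out of 4) on item 3.8 (leg agility) and/or item 3.14", but such a participant may also score 0 on items 3.9 and 3.10. The floor therefore does not separate the two scores, and a minimum says nothing about the baseline mean, which is not given.
- *Power falls to 0.40.* That needs the difference to shrink to 1.38 while the SD stays at 2.5. In the equal-item model the SD falls to 1.94 at r = 0 and 1.58 at r = 0.5.

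**Conclusion.** The point holds as an internal inconsistency. The Sample Size section names one set of items as the primary outcome, and the outcome and analysis sections define and test another. The stated 0.80 power is therefore not established for the 0-12 score. This is not an arithmetic error, since 40 participants follow from the inputs quoted.

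The condition for the claim to hold is a standardized effect on the 0-12 score of about 0.91 (20 per arm) or 0.84 (23 per arm), and this rests only on the t-test and alpha 0.05. The illustrative range for r from 0 to 0.5, namely 0.59 to 0.77 with 20 per arm and 0.66 to 0.83 with 23, also rests on five equally weighted ratings with equal effects and a common correlation. It shows how sensitive the figure is and does not estimate the trial's power. A reader might infer that the trial is underpowered. The article does not establish that either way.

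**What to change.** Before unblinding:

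1. Reconcile the Sample Size section with the Primary Outcome Measure and Statistical Analyses sections, which already agree on the lower limb score. If the definition changed at some point, say when and why.
2. State on which score the previous trial measured -2.3 (SD 2.5).
3. Withdraw the 0.80 power claim for the 0-12 score unless that effect is justified for it.
4. State what the enrolled sample can detect with 0.80 power: about 0.84 SD if all 46 are analysed in a near-equal split, and about 0.92 SD with 39 completers. Simple randomization does not guarantee an equal split, so use the actual arm sizes (18 and 28, for example, would give about 0.87 SD).
5. Convert this to points with a blinded pooled SD of the 0-12 score, and say whether it is the SD of raw scores or of change from baseline.

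The cost is a change of wording and one blinded SD calculation. No more participants are needed. The drawback is that the stated power may look less favourable.

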## Methods

### Design

A superiority parallel-group randomized controlled trial, 1:1 allocation, blinded assessments, and intention-to-treat analysis, will be performed in a community-based setting in the city of Belo Horizonte, Brazil. All participants will be informed of the study procedures and will provide written consent. Participants will be randomly assigned to the experimental or control group. Figure 1 shows the schedule of enrollment, interventions, and assessments [23]. Both groups will undertake intervention sessions of 60 minutes 3 times per week over 12 weeks [15]. Individual interventions will be performed at home and supervised remotely by a physiotherapist. Outcome measures will be collected at the Universidade Federal de Minas Gerais laboratory at baseline (week 0), after the intervention (week 12; primary time point), and at the 4-week follow-up (week 16; secondary time point) by the same examiner (Figure 2). This protocol has been developed in accordance with the SPIRIT (Standard Protocol Items: Recommendations for Interventional Trials) guidelines. This trial was registered at ClinicalTrials.gov (NCT06646523).

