### Randomization

The randomization sequence will be computer-generated using a simple randomization method, in which each participant has an equal probability of being assigned to the experimental or control group. The sequence will be prepared prior to the start of the study by a trained research assistant who will not be involved in the study. The allocation will be maintained in sequentially numbered, sealed, opaque envelopes and stored in a locked cabinet and will not be accessible to investigators responsible for recruitment and assessment. After completion of the baseline assessment, the training therapist will open the next envelope in sequence to reveal the group allocation. Eligible participants will be randomly allocated to either the experimental or control group.

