## Results

Recruitment began in October 2024 and concluded in October 2025. A total of 46 participants were enrolled in the study. Data collection is currently in the follow-up phase. Upon completion of follow-up assessments, data collection will be finalized. Data analysis has not yet been performed. We anticipate that the results will be compiled and submitted for publication by May 2026.

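### The 15% dropout allowance is computed as 40 × 1.15 = 46 instead of 40/0.85 = 47.06, so 46 recruited covers about 13% loss; the effect on power is minor

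*Protocol article*

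**What the plan says.** The Sample Size section takes its effect from an earlier trial, "reporting a mean difference of –2.3 (SD 2.5), a sample size of 40 participants was required", with the aim "to achieve a power of 0.80 at a 2-tailed significance level (α=.05". It then allows for loss: "Assuming a dropout rate of 15%, 46 participants will be recruited (23 per group". The inflation formula is not shown.

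The Design section gives a 1:1 ratio. The Randomization section describes a "simple randomization method, in which each participant has an equal probability of being assigned to the experimental or control group" and mentions no blocks or other restriction. The Results section reports: "A total of 46 participants were enrolled in the study". It also says that recruitment has ended and that no analysis has been done.

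**The concern.** A stated dropout rate is a fraction of the people who enter the trial. To keep 40 after losing 15%, the requirement must be divided by 0.85. Multiplying by 1.15 adds 15% of the completers instead, and always gives too small a number. The sentence therefore promises a combination (40 completers, 15% dropout, 46 recruited) that does not fit together.

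What is at stake is whether the published justification is correct and, if power falls short, by how much. A second, smaller matter is that the sentence gives an exact arm size, whereas the randomisation method makes arm size random.

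**Working it through.** **Inputs.** All come from the protocol article. Sample Size: difference 2.3, SD 2.5, power 0.80, two-sided α = 0.05, requirement 40, dropout 15%, recruited 46. Design: 1:1 allocation. Randomization: simple, equal probability for each participant.

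**Step 1: reproduce the 40.** Standardised effect d = 2.3/2.5 = 0.92. Power of the two-sample t test comes from the noncentral t distribution with n₁ + n₂ − 2 degrees of freedom and noncentrality d/√(1/n₁ + 1/n₂).
- 19 per arm: power 0.788.
- 20 per arm: power 0.809.

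So 20 per arm, 40 in total, is the smallest equal-arm size that reaches 0.80. The plan's 40 reproduces exactly.

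**Step 2: reproduce the 46.** 40 × (1 + 0.15) = 46. This matches exactly.

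**Step 3: the inflation that 15% dropout requires.** 40/(1 − 0.15) = 40/0.85 = 47.06, which rounds up to 48 in equal arms.

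**Step 4: what 46 delivers.**
- Expected completers at 15% loss: 46 × 0.85 = 39.1. With 48 it would be 48 × 0.85 = 40.8.
- Loss that still leaves 40: 1 − 40/46 = 13.0%.
- If each participant independently has an 85% chance of completing, the probability of at least 40 completers is 0.45 with 46 recruited and 0.71 with 48.

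**Step 5: effect on power** (t test on completers, d = 0.92).

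| Completers | Split | Power |
|---|---|---|
| 40 | 20/20 | 0.809 |
| 40 | 17/23 | 0.800 |
| 39 | 19/20 | 0.799 |
| 39 | 17/22 | 0.792 |
| 39 | 15/24 | 0.777 |
| 39 | average over Binomial(39, 0.5) splits | 0.788 |
| 46 (no loss) | 23/23 | 0.862 |
| 46 (no loss) | 19/27 | 0.852 |

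When the number of completers is also allowed to vary at random, average power under simple randomisation is 0.788 for 46 recruited and 0.806 for 48.

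**Step 6: arm sizes.** Under Binomial(46, 0.5), exactly 23 in each arm has probability 0.117. It is the most likely split, but the method does not guarantee it.

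**The case against.** The strongest reply is that nothing of consequence follows. The shortfall is 40 − 39.1 = 0.9 of a completer, and 0.799 rounds to the 0.80 claimed. Even the average over random splits is only 0.80 − 0.788 = 0.012 below target, which is small beside the uncertainty in the assumed effect and SD. This stands, and it is why the point is minor.

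A second reply is that 46 can be reached correctly by another route. The normal approximation needs 19 per arm, and 19/0.85 = 22.35 rounds up to 23 per arm. The article does not say this. It gives 40 as the requirement, which is the t-test answer, and 46 must be judged against that base.

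A third reply is that counting completers is only a benchmark. The Statistical Analyses section plans an intention-to-treat analysis with a random-intercept model over three time points and a strategy for missing data, so a participant who misses week 12 need not drop out of the analysis altogether. That is fair. Any gain in power from this cannot be computed from the article. The sample-size sentence itself, however, makes an allowance for dropout, and that allowance is miscalculated.

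A reader might also infer three stronger things, which the document does not support:
- **That the power depends on balanced arms.** It does not: 40 completers split 17/23 still give 0.800, and with all 46 observed even 19/27 gives 0.852.
- **That the Randomization and Sample Size sections contradict each other.** The figure of 23 reads naturally as the planned or expected size under 1:1 allocation, and neither section claims that equality is guaranteed.
- **That a realised 23:23 split would cast doubt on simple randomisation.** It is the single most likely result of that method, and the article reports no realised arm sizes.

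**Conclusion.** The point holds as a minor arithmetic error. The plan multiplied by 1.15 where it should have divided by 0.85. Under its own inputs, 46 recruited covers about 13% dropout; at the stated 15% it leaves about 39 expected completers, one short of 40. Power is then about 0.80 (0.799) with near-equal arms and about 0.79 (0.788) averaged over simple-randomisation splits. The trial should not be called underpowered on this ground.

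These figures assume a two-sample t test on completers, dropout unrelated to arm, and that the SD of 2.5 is the SD of the quantity compared between groups, which the article does not specify.

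**What to change.** Recruitment is closed, so no change in enrolment is asked for. In the Sample Size section, replace the dropout sentence with, for example: *46 participants allow for about 13% dropout; at 15% dropout, about 39 completers give power of about 0.79 to 0.80 under the stated assumptions.*

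In the same sentence, describe the arms as about 23 expected per group, because simple randomisation does not fix their size. If the sequence was in fact restricted, for example blocked, correct the description in the Randomization section instead.

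The cost is one or two sentences and a very slightly less favourable power statement. Design and analysis are unaffected. The correction is best made now, before the data are analysed, so that the results paper does not repeat the error.

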### Statistical Analyses

All statistical analyses will be performed by an independent examiner blinded to group allocation using SPSS for Windows (IBM Corp). Baseline characteristics will be summarized by treatment group using descriptive statistics. Means (SD) or median (IQR) will be used for continuous variables according to analysis of normality (Shapiro-Wilk test). Frequency (percentage) will be used for categorical variables.

All analyses will follow the intention-to-treat principle, including all randomized participants in the groups to which they were originally allocated. The primary outcome will be the lower limb bradykinesia score, with the primary end point defined as the postintervention assessment at 12 weeks. Analytic approaches will be used to handle missing data, as recommended by Jakobsen et al [37]. The specific procedure will depend on the proportion of missing data, as stated by Jakobsen et al [37]. The statistical models will include a random intercept for participants and fixed effects for time (before intervention, after intervention, and follow-up), group (intervention and control), and group-by-time interaction. The primary analysis will focus on the group-by-time interaction effect. The level of significance will be set at 5%. Effect estimates will be reported considering the CIs (95% CI) for the between-group mean differences at each time point (week 12 minus week 0 and week 16 minus week 0). Secondary outcomes will be considered exploratory. Where applicable, adjustment for multiple comparisons will be performed using the Bonferroni method [38].

Adverse events will be summarized descriptively by treatment group, including the number and proportion of participants experiencing at least one event, as well as the frequency and severity of events.

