**Methods:**

A randomized controlled trial will be performed with 1:1 allocation, blinded assessments, and an intention-to-treat analysis. Altogether, 46 individuals with PD, aged ≥50 years, who have bradykinesia and a sedentary or insufficiently active lifestyle, will be included. Participants will be randomly assigned to either (1) an experimental group (high-speed bodyweight resistance training) or (2) a control group (bodyweight intervention; usual speed). Both groups will perform a home-based, remotely supervised intervention, consisting of 60-minute individual sessions, 3 times per week over 12 weeks, with a trained physiotherapist. The primary outcome is bradykinesia of the lower limbs. The secondary outcomes are mobility, muscle power, dynamic balance, and quality of life. The effects of the training will be analyzed from the collected data by using the intention-to-treat analysis. Between-group differences will be measured by 2-way repeated measures ANOVA, considering the baseline, posttraining follow-up (primary time point), and 4-week follow-up (secondary time point).

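### With only a random intercept stated, one correlation serves visit gaps of 12 and 4 weeks, so the week-12 standard error can be too small or too large

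*Protocol article*

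**What the plan says.** The Statistical Analyses section describes the model this way: "The statistical models will include a random intercept for participants and fixed effects for time (before intervention, after intervention, and follow-up". Group and the group-by-time interaction complete the fixed effects. On the test it says: "The primary analysis will focus on the group-by-time interaction effect". The primary outcome is the lower-limb bradykinesia score, "with the primary end point defined as the postintervention assessment at 12 weeks". Estimates with 95% confidence intervals are to be given for "between-group mean differences at each time point (week 12 minus week 0 and week 16 minus week 0". The Design section places assessments "at baseline (week 0), after the intervention (week 12; primary time point), and at the 4-week follow-up (week 16; secondary time point".

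The Methods paragraph of the Abstract names a different procedure: "Between-group differences will be measured by 2-way repeated measures ANOVA". Neither place names a residual covariance structure, a robust standard error, a degrees-of-freedom method or a sphericity correction. Neither rules one out.

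**The concern.** A random intercept with independent residuals gives every visit the same variance and every pair of visits the same correlation. Here the pairs differ. Weeks 0 and 12 are separated by the whole training period, weeks 12 and 16 by four weeks without training. If participants respond differently to training, the correlation across the training period falls, while scores four weeks apart may stay close.

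The model pools all three pairwise differences into one error term and uses it for every within-participant contrast. The standard error of the week-12 effect therefore depends partly on how scores behave between weeks 12 and 16, which has no bearing on that effect. What is at stake is the coverage of the primary 95% interval and the true level of the test declared at 5%.

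**Working it through.** **Inputs from the protocol article.** Visits at weeks 0, 12 and 16; random intercept; fixed time, group and interaction; 5% level; 23 per group. Group size comes from the Sample Size section, and its 40 is reproduced: 2.3/2.5 = 0.92, a two-sample t-test at two-sided 5% and 80% power needs 19.55 per group, so 20 per group (power 0.809). Then 40 x 1.15 = 46.

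**Inputs assumed.** The three correlations r(0,12), r(0,16), r(12,16) and the visit variances. The documents give none of them.

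**Formula.** With complete balanced data, the ratio of the model standard error to the true one for week 12 minus week 0 is

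ratio = sqrt( average of the three pairwise-difference variances / Var(Y12 - Y0) ).

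With equal variances this becomes sqrt( (1 - mean r) / (1 - r(0,12)) ). The standard error is too small exactly when r(0,12) < [r(0,16) + r(12,16)]/2.

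**Time-decaying correlation.** Let x be the 4-week correlation, so the three correlations are x^3, x^4 and x. The condition is 2x^3 < x^4 + x, or x^3 - 2x^2 + 1 > 0, or (x - 1)(x^2 - x - 1) > 0. Both factors are negative for 0 < x < 1, so it always holds.

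**Three cases by hand.**
- (.5, .5, .8): mean r = 0.60; sqrt(0.40/0.50) = 0.894.
- (.7, .4, .8): mean r = 0.633; sqrt(0.367/0.30) = 1.106.
- (.6, .6, .7) with week-16 variance 1.5: difference variances 0.800, 1.030 and 0.785, average 0.872; sqrt(0.872/0.800) = 1.044.

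**Simulated type I error, week-12 contrast.** 23 per group, 40,000 null trials per row. The pooled-error test has 88 df. The change-score test, which is what an unstructured covariance gives with complete data, has 44 df.

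| r(0,12), r(0,16), r(12,16) | SE ratio | Random intercept | Unstructured |
|---|---|---|---|
| .7, .7, .7 | 1.000 | 5.0% | 5.0% |
| .65, .65, .75 | 0.951 | 6.2% | 4.9% |
| .6, .55, .8 | 0.935 | 6.7% | 5.0% |
| .6, .6, .8 | 0.913 | 7.4% | 5.0% |
| .5, .5, .8 | 0.894 | 7.9% | 5.0% |
| .5, .5, .9 | 0.856 | 9.2% | 5.1% |
| decay, x = .9 | 0.938 | 6.6% | 4.8% |
| decay, x = .8 | 0.934 | 6.8% | 5.0% |
| .7, .4, .8 | 1.106 | 3.1% | 4.9% |
| .7, .5, .75 | 1.080 | 3.5% | 5.0% |
| .6, .6, .7, week-16 variance 1.5 | 1.044 | 4.0% | 4.9% |

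In the last three rows weeks 12 and 16 are still the most correlated pair, yet the week-12 standard error is too large. In those rows the week 16 minus week 0 standard error is too small (ratios 0.782, 0.837 and 0.920).

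**Interaction test (2 df), 20 per group.** Patterns (.5, .5, .8), (.6, .55, .85), (.5, .45, .9) and (.7, .65, .85) gave 6.0%, 6.2%, 7.0% and 5.7%. Patterns (.7, .4, .8) and (.7, .5, .75) gave 6.7% and 5.9%.

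**The case against.** First, the article says what the models will include; it does not say that nothing else enters. A residual structure can be fitted alongside a random intercept, and a journal article may leave that to a fuller plan. This stands as a limit: the defect follows only if the stated model is fitted with independent residuals. It does not dispose of the point. The random intercept is a stated choice, and the Abstract's alternative rests on sphericity unless corrected, so following either text as written leads to the same place.

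Second, a reader might infer that the primary interval is simply too narrow because weeks 12 and 16 are close together. The documents do not support that. They give no correlations, and closeness of the last two visits is not sufficient, as the last three rows of the table show. Uneven loss of benefit after training stops could produce such a pattern.

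Third, the primary analysis is the interaction, not a single contrast, and its distortion is smaller. That is correct. The larger rates apply to the week-12 interval and to any test at the declared primary time point.

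Fourth, the section allows Bonferroni adjustment where applicable. If it were applied to the two reported contrasts in the first four interaction patterns above, week 12 would be rejected in 3.3% to 4.9% of null trials. Each such test should then run at 2.5%, and the family-wise rate is still about 6.6% to 7.7%.

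**Conclusion.** The concern holds in conditional form. As described, and with independent residuals, the model assumes equal variances and one common correlation across unequally spaced visits, and the week-12 standard error is right only if the week 0-to-12 change has the average variance of the three differences. Over the assumed patterns the standard error ranges from about 14% too small to about 11% too large. The direction in this trial cannot be settled from the documents. Too small is the expected direction if correlation decays with time, or if both follow-up visits correlate equally with baseline and more strongly with each other. The test then runs at about 6% to 9%. The distortion is moderate, but it falls on the primary estimate and is cheap to remove, so the plan should be changed. The figures assume complete, normally distributed data.

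**What to change.** Before the analysis, which the Results section reports as not yet done, replace the random intercept with an unstructured 3x3 residual covariance over the three visits (in SPSS, MIXED with REPEATED and COVTYPE(UN)), with Satterthwaite or Kenward-Roger degrees of freedom. Name one fallback structure, for example heterogeneous Toeplitz, to be used only for non-convergence. Rewrite the Abstract so that it describes the same model. This works whichever way the correlations fall: the unstructured analysis stayed at 4.8% to 5.1% in every row of the table.

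The cost is one line of specification, six covariance parameters instead of two, fewer error degrees of freedom (44 against 88 with complete data on 46 participants) and often slightly wider intervals. Six parameters are estimable with the 39 to 46 participants expected (46 x 0.85 = 39.1 at the planned 15% dropout).
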